### Outcome measures

A visual analogue scale (VAS) for measuring pain [43]. A pain scale is a tool that doctors use to help assess a patient’s pain level. A person usually self-reports pain using a specially designed scale, sometimes with the help of a doctor, parent, or guardian. The pain scale may be used on admission to the hospital, during a doctor’s visit, during physical activity, or after surgery. Visual analogue scale or VAS is the pain ruler that includes a horizontal line that is graded from 0 to 10, where 0 indicates absolute painlessness and 10 indicates unbearable pain. At one end is “no pain” and at the other end is “the worst pain” or “indescribable pain.” The person puts a cross X on the line to indicate the intensity of their pain. A doctor then measures the line with a ruler to obtain a pain score.The Depression, Anxiety, and Stress Scale (DASS-21) will be is used to measure depression and stress. The questionnaire contains 21 items (7 items per each component). The depression subscale includes phrases that measure unhappy mood, lack of self-confidence, hopelessness, worthlessness of life, lack of interest in involvement in affairs, lack of enjoyment of life, lack of energy, and empowerment. The anxiety subscale has expressions that attempt to assess physiological hyperarousal, fears, and situational anxieties, and the stress subscale includes terms such as difficulty in achieving relaxation, nervous tension, irritability, and restlessness [44].The HBM questionnaire: as indicated earlier a self-designed questionnaire specifically will be developed for the study including items covering knowledge, perceived severity, perceived sensitivity, perceived benefit, perceived barriers, self-efficacy, and cues to action. Various statements will be included in the questionnaire based on previous studies on elderly musculoskeletal pain. The psychometric characteristics of the questionnaire, including quantitative and qualitative face validity, quantitative and qualitative content validity, construct validity, and reliability, will be assessed. To assess the validity of the statements, 10 elderly people will be involved, and the formal validity of the statements will be done. To determine the content validity ratio (CVR), the index designed by Lawshe [45] is used and to calculate the content validity index (CVI) the method of Bausell Waltz is used [46]. The questionnaire will be given to 15 specialists (10 health education specialists, 2 physiotherapists, 2 psychologists, and 1 general practitioner) to measure the CVI and CVR. Quantitative and qualitative face validity of the article will be done. Exploratory factor analysis will be used to assess the construct validity. In order to determine Cronbach’s alpha coefficient, a questionnaire is given to 30 elderly people with inclusion and exclusion criteria. Afterwards, we use construct validity to confirm the dimensions of the tools and items, during which path analysis and exploratory factor analysis are used. After exploratory factor analysis, dimensions and items would be determined.In addition, demographic data including age, sex, education, BMI, and history of disease will be collected.The behavior questionnaire, which includes three behaviors (vitamin D consumption, physical activity, and stress management), filled out by the elderly before and after the intervention.

Data will be collected using the study measures. The outcomes will be assessed in four points in time: before, immediately, 3, and 6 months after the interventions. Questionnaires of behavior and health belief model are measured with a 5-point Likert scale from completely disagree to completely agree.

### Data management

Participants’ personal information is assigned a unique identification code, stored in a password-protected format, and accessible only to the principal investigator. Participants cannot be identified in manuscripts, reports, or research-related presentations. Data that will be entered into SPSS will be double checked to promote data quality.

### Data analysis

To conduct statistical analysis of data, the IBM SPSS Modeler version 21 will be used. Descriptive statistics such as frequency and percentage, mean, and standard deviation will be used. For classification variables, chi-square and Fisher’s exact tests will be used to determine the difference between groups. Before and after evaluation, intra-group comparisons are determined by paired *t*-test. Independent group means will be evaluated with a 95% confidence interval. The Kolmogorov-Smirnov test will be used to check the normality of data. Finally, after adjusting for gender and age group, a multivariable linear regression model will be used to examine the combined effects of vitamin physiotherapy and social-psychological interventions on changes in pain scores. Repeated measure analysis of variance will also be used. This study will use exploratory factor analysis to identify the underlying categories of an item set.

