### Study setting

The study will be carried in a nursing home in Tehran, Iran. There is evidence that usually a sample of people living in Tehran would be a representative of Iranian population [36, 37].

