### Sampling

For sampling in the first stage, Tehran will be divided into four clusters of north, south, east, and west. A lottery method will be used to select nursing homes in each cluster, by assigning a number to each nursing home. The numbers will be written on a card, which will be placed in a container and thoroughly mixed. Two cards are then selected, one card representing the intervention group and the other representing the control group. The intervention and control groups (each consisting of 15 individuals) are selected from elderly homes according to the criteria for identification and selection. The reason for sampling from all four clusters is to generalize the results to the entire population.

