### Blinding

This study is not blinded. The main investigator is a health education specialist who manages the data. Allocation of people to intervention and control groups will be done randomly (lottery).

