## Discussion

This study aims to design a multidisciplinary educational intervention based on health belief model (HBM) for elderly residents of nursing home. One of the features of this study is its focus on improving the health of elderly residents in nursing homes. Considering that elderly suffer from various diseases such as musculoskeletal pain, the main purpose of this study was to design a multimodal intervention based on HBM to obtain preventive behaviors of musculoskeletal pain in the elderly. The positive effect of interventions on teachers [47] as well as combined programs (supplement consumption and physical activity) based on HBM [48] has been proven. Various studies have also confirmed the positive effect of HBM-based interventions [49, 50] and the effect of multimodal interventions on reducing pain in the elderly [51]. The current study might provide similar findings. Different programs have been designed in various countries to reduce musculoskeletal pain, such as the multidisciplinary rehabilitation programs in Germany that aim to improve the performance and workability of individuals [52, 53]. In the USA, the National Institute of Health has allocated a budget for musculoskeletal conditions [3]. Routine care is provided for the elderly in healthcare centers in Iran, but there is no specific care for preventing and controlling musculoskeletal disorders, and in elderly care centers may not be provided due to lack of compliance with health standards [54]. Even in the interventional researches that are done on the elderly population, the elderly group living in the nursing home is eliminated [55]. Also, in most research related to physical activity, the elderly is left out due to age-related diseases [56]. Therefore, the strengths of this study we can mention the combined intervention to reduce musculoskeletal pain in the elderly living in nursing homes and the group interaction of the elderly in the intervention group, which reduces stress and follows the educational program. Also, sampling from several centers and the presence of a control group that only receive routine interventions are other strengths of this study, because the elderly care status can be improved if the results of this study will be positive.

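### Whole nursing homes are drawn into the arms, but every between-arm method named in the Data analysis section treats residents as independent

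*Protocol article*

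**What the plan says.** **Allocation.** The Sampling section first forms regions: "Tehran will be divided into four clusters of north, south, east, and west". Homes are then drawn: "A lottery method will be used to select nursing homes in each cluster, by assigning a number to each nursing home". The draw also fixes the arm: "Two cards are then selected, one card representing the intervention group and the other representing the control group". Group size follows: "The intervention and control groups (each consisting of 15 individuals) are selected from elderly homes according to the criteria for identification and selection".

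**Competing wording.** The Blinding section says "Allocation of people to intervention and control groups will be done randomly (lottery", and the Study setting section says "The study will be carried in a nursing home in Tehran, Iran". The Discussion counts as strengths "sampling from several centers and the presence of a control group that only receive routine interventions are other strengths of this study", and the Recruitment section also refers to homes in the plural. No procedure for randomising individual residents is described.

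**Analysis.** The Data analysis section names, for comparing arms:
- chi-square and Fisher's exact tests
- independent means: "Independent group means will be evaluated with a 95% confidence interval"
- a linear regression for change in pain, adjusted for gender and age group
- repeated-measures ANOVA

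None of these includes home or region. The Trial design section calls the study a parallel-group trial, and the word cluster is used only for the four regions.

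**The concern.** When homes are allocated, the arm comparison is a comparison of four homes with four homes. Residents of one home are likely to resemble each other. The Intervention section has sessions held in the home, the psychological ones as group discussions, and a home employee handing out the tablets. The Limitations section admits that conditions in the homes cannot be controlled.

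A resident-level analysis counts 60 independent people per arm and leaves the variation between homes out of the standard error. A chance difference between two sets of four homes can then be reported as an effect on pain, the primary outcome, or on the DASS-21 and health belief scores.

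This is not a detail left to a separate analysis plan. The article names the methods and the adjustment covariates, and they do not fit the allocation it describes.

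**Working it through.** **1. Does the stated sample size fit whole-home allocation?** Sampling: 4 regions, 1 home per arm per region, 15 residents per home. 4 × 15 = 60 per arm, which is exactly the enrolled number in the Sample size section. Total: 8 homes, 120 residents.

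**2. The plan's 55 per group.** No effect size or SD is given, so 55 cannot be reproduced directly. Solving n = 2(1.960 + 0.842)²/d² for n = 55 gives d = 2.802 × √(2/55) = 0.534 SD (two-sided 5%, 80% power). This uses no design effect.

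**3. Error of a resident-level comparison.** The ICC ρ is an assumption, with range 0.01 to 0.10. Let f be the share of ρ common to the two homes of a region, also an assumption. That share cancels in the arm difference. With m = 15:

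- true variance ÷ variance assumed by the naive test ≈ 1 + 14ρ − 15fρ = DE
- type I error ≈ 2 × [1 − Φ(1.96/√DE)]

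With no regional share (f = 0):

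| ICC | DE | SE understated by | Type I, formula | Type I, simulated |
|---|---|---|---|---|
| 0.01 | 1.14 | 1.07 | 6.6% | 6.7% |
| 0.02 | 1.28 | 1.13 | 8.3% | 8.4% |
| 0.05 | 1.70 | 1.30 | 13.3% | 13.5% |
| 0.10 | 2.40 | 1.55 | 20.6% | 21.0% |

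The simulations used 40,000 null trials per ICC. Nominal 95% intervals then cover about 93%, 87% and 79% at ICC 0.01, 0.05 and 0.10.

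With a regional share:

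| f | DE at ICC 0.01 / 0.10 | Type I, formula |
|---|---|---|
| 0.5 | 1.065 / 1.65 | 5.7% / 12.7% |
| 0.8 | 1.02 / 1.20 | 5.2% / 7.4% |

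Simulation at ICC 0.10 gives about 13% and 7.7%. DE reaches 1 when 15f = 14, that is when about 93% of the ICC is regional. A t-test on the four within-region differences of home means held about 5% in every case simulated.

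**4. Power once homes are respected.** With 60 per arm and d = 0.534, SE = √(2 × DE/60), f = 0 and a noncentral t distribution. Without region in the model there are 8 − 2 = 6 degrees of freedom. With region there are 8 − 2 − 3 = 3.

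| ICC | SE (SD units) | d/SE | Power, 6 df | Power, 3 df |
|---|---|---|---|---|
| 0.01 | 0.195 | 2.74 | 63% | 47% |
| 0.05 | 0.238 | 2.24 | 47% | 35% |
| 0.10 | 0.283 | 1.89 | 36% | 26% |

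Even at ICC 0, power is 69% (6 df) or 51% (3 df), so the small number of homes costs power by itself.

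**The case against.** **The unit of allocation is not stated consistently.** The Blinding section speaks of allocating people, and Study setting of one home. A reader might infer an individually randomised trial, for which the named methods would be ordinary. The documents do not support that. The only lottery described draws homes, several homes are mentioned elsewhere, and 4 × 15 reproduces 60 per arm. The inconsistency still has to be removed.

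**The error may be small.** This stands in part. No ICC is given, the low end of the assumed range gives only 6.7%, and pairing within regions removes whatever the two homes share. The regression also models change in pain, whose ICC may differ from that of a single score. A reader might infer that type I error is certainly far above 5%, but the documents do not establish that. The direction is clear unless nearly all of the between-home variation is regional.

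**Not every listed procedure is affected in this way.** This stands. The paired t-tests compare times within a group, and the exploratory factor analysis is not a treatment comparison. Repeated-measures ANOVA handles correlation within a person but not within a home. The point is limited to between-arm inference.

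**The remedy is expensive.** This also stands. With 8 homes the change is more than a matter of wording, because the stated power goes with it.

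**Conclusion.** The point holds for between-arm inference. The allocation described is by home within region, and the between-arm methods named ignore both.

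The size is conditional on assumptions the documents cannot settle: type I error of about 6.7% to 21% for an ICC of 0.01 to 0.10 with no regional similarity, and about 5% to 13% if half or more of the ICC is regional. It would be wrong to infer that the trial's p-values are badly inflated whatever the ICC, or that every listed analysis fails.

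The correction is needed before analysis because it affects the primary pain comparison and both sets of secondary outcomes. It also shows that 80% power does not hold for this design.

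**What to change.** 1. State once that the nursing home is the unit of allocation, one per arm within each of four regions, and call the trial cluster-randomised and stratified by region. Reconcile Study setting and Blinding with Sampling.
2. Analyse VAS, DASS-21 and the health belief scores with a mixed model containing a random home effect, region as a stratum and, for repeated visits, the correlation within a person. Keep the home effect even if its variance is estimated at zero. Base the degrees of freedom for the arm effect on the number of homes (3 with region fitted), so that a zero estimate does not restore resident-level precision.
3. Add a supporting t-test on the four within-region differences in home means, and say in advance that the model is primary. A permutation test on four pairs cannot serve as the check: its smallest two-sided p-value is 2/16 = 0.125.
4. Restate the power calculation with an assumed ICC, its source and the number of homes.

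**Cost.** Intervals widen. At the implied 0.53 SD, power is about 26% to 63% over the assumed ICC range, assuming no gain from pairing by region; real regional similarity would recover some of it. If homes can still be added, more homes would help. If not, the article should say that the trial can detect only larger differences.

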## Background

Musculoskeletal disorders (MSDs) include over 150 diseases, which are characterized by conditions ranging from fractures, sprains, and strains to lifelong disabilities and usually with pain (often chronic), limited mobility, skill, and overall performance levels. Osteoarthritis, rheumatoid arthritis, osteoporosis, and other diseases are among the most common of these disorders [1–3]. Approximately 1.71 billion people have MSDs worldwide [2].

In 2022, there were 771 million people aged 65 years or over globally, 3 times more than the size in 1980 (258 million). The older population is projected to reach 994 million by 2030 and 1.6 billion by 2050 [4]. Iran has been argued that this country had the highest increase in the burden of MSDs over the past three decades worldwide [5]. Behavioral factors such as inactivity and repetitive movements, as well as non-behavioral factors such as aging, gender, and genetics, are involved these disorders [6]. Pain is one of the most noticeable symptoms of these disorders. Studies show that the elderly suffer from musculoskeletal pain [7, 8]. Inactivity [7], stress and depression [9], and vitamin D deficiency [10–13] can be mentioned among the causes of MSDs.

Control of MSDs in the elderly is crucial because it usually leads to disability and a reduction in their quality of life [14–16]. There are different types of methods for reducing pain, such as nutrition (vitamin D intake), physiotherapy, exercise, and stress management [12, 17–20]. Despite the proven effectiveness of many pain-reducing methods, adherence to these methods in old people is an important challenging issue due to disease characteristics and poor individual perception.

One of the inevitable changes of old age is cognitive and perceptual changes, which have negative effects on the quality of life of the elderly. One of the perceptual changes in the elderly that influences inactivity is the fear of falling [21]. Low self-confidence and low self-efficacy [21], as well as their lower knowledge and awareness [22] about the benefits of physical activity, is a big obstacle among elderly people. Different chronic diseases in old age is another issue [23] that could be contributed to inactivity in this age group. Immobility and movement phobia caused by fear, lack of knowledge about the benefits of vitamin D consumption, low income, and inability to buy and cook healthy food are among the reasons for vitamin D deficiency in old people [24].

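### Cheap improvement: prespecify baseline DASS-21 depression and stress scores in the adjusted pain model, which now names only gender and age group

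*Protocol article*

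**What the plan says.** The Data analysis section of the protocol article states: "Finally, after adjusting for gender and age group, a multivariable linear regression model will be used to examine the combined effects". The effects in question are those of the intervention components, including the "social-psychological interventions on changes in pain scores", so the outcome is change in pain. Gender and age group are the only adjustment variables named. The section adds "Repeated measure analysis of variance will also be used", with no covariates stated.

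Other baseline information is available. Under Outcome measures, "The Depression, Anxiety, and Stress Scale (DASS-21) will be is used to measure depression and stress", and on timing, "The outcomes will be assessed in four points in time: before, immediately, 3, and 6 months after the interventions". Psychological distress is a secondary outcome, so a pre-intervention DASS-21 score will exist for each resident assessed. The Background gives distress a causal role, listing as causes of these disorders "Inactivity [7], stress and depression [9], and vitamin D deficiency".

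The Sampling section draws two homes by lottery in each of four areas of Tehran, one for each arm, and describes 15 residents per group being selected from the homes. The Blinding section says the study is not blinded.

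**The concern.** The protocol's own rationale treats distress as a driver of the condition, measures it at baseline, and then leaves it out of the pain model without giving a reason. Two things could be at stake.

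- **Precision.** If baseline distress predicts pain change, including it narrows the interval for the primary effect.
- **Comparability.** With four homes per arm, and residents apparently chosen once a home's group is known, the arms may differ in distress for reasons other than chance. A standard error calculated on residents does not cover selection.

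Prespecification also matters. If an imbalance in distress appears, an unblinded team would have to decide whether to adjust after seeing the data.

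**Working it through.** **Inputs from the protocol.** Confidence level 95%, power 80%, 55 per group, raised to 60 for 10% dropout (Sample size); 15 residents per home, hence 4 × 15 = 60 per arm in 8 homes (Sampling).

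**Assumptions.** Two-sided test; extra R² of baseline distress for pain change; intracluster correlation (ICC) of distress within homes; correlation r between distress and pain change. The protocol gives none of these.

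**1. The plan's own figure.** The 55 cannot be reproduced, because no effect size or SD is stated. Solved backwards, it implies a standardised difference of (1.960 + 0.842) × √(2/55) = 0.534. The step from 55 to 60 is close to the usual inflations: 55/0.9 = 61.1 and 55 × 1.1 = 60.5.

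**2. Precision.** A covariate with extra R² multiplies the standard error by √(1 − R²). Extra terms cost degrees of freedom. With about 110 analysed and four parameters already fitted (intercept, arm, gender, age group taken as two levels), the residual degrees of freedom are 106. Two added terms multiply the standard error by √(106/104) = 1.010. Power is Φ(2.802 / SE ratio − 1.960).

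| Extra R² (assumed) | SE ratio | Power | SE ratio with 2 extra terms | Power with 2 extra terms |
|---|---|---|---|---|
| 0 | 1.000 | 80.0% | 1.010 | 79.3% |
| 0.02 | 0.990 | 80.8% | 0.999 | 80.1% |
| 0.03 | 0.985 | 81.2% | 0.994 | 80.5% |
| 0.05 | 0.975 | 82.0% | 0.984 | 81.3% |
| 0.10 | 0.949 | 84.0% | 0.958 | 83.3% |

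With four added terms the cost is √(106/102) = 1.019, about 4% in variance. At R² = 0.03 the ratio is then 0.985 × 1.019 = 1.004, so the gain has gone.

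**3. Imbalance.** The SD of the standardised difference in a baseline covariate between arms is √((2/60) × (1 + 14 × ICC)). A typical (one-SD) imbalance shifts the pain effect by r times that; r = 0.2 is used here.

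| ICC (assumed) | SD of imbalance | Chance of a gap above 0.25 SD | Shift at r = 0.2 (pain SDs) |
|---|---|---|---|
| 0 | 0.18 | 17% | 0.04 |
| 0.05 | 0.24 | 29% | 0.05 |
| 0.10 | 0.28 | 38% | 0.06 |
| 0.20 | 0.36 | 48% | 0.07 |

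These shifts compare with an implied design effect of 0.53 SD and a resident-level standard error of √(2/55) = 0.19 SD. They describe chance imbalance only. An imbalance produced by selection could be larger, and nothing in the protocol allows it to be sized.

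**4. For scale.** An outcome ICC of 0.05 with 55/4 = 13.75 analysed per home gives a design effect of 1 + 12.75 × 0.05 = 1.64 and lowers power from 80% to about 59%. Home matters far more in this model than distress does.

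**The case against.** The case against is strong, and much of it stands.

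- **The chosen covariates have support.** The Background names ageing and gender among the factors involved in these disorders. A short prespecified list is legitimate, and nothing in it is wrong or contradictory.
- **Prognostic strength is unknown.** The Background calls stress and depression causes of the disorders, not predictors of change in VAS. No R² or correlation is given, so any gain is assumed.
- **Chance imbalance is already covered.** Under random allocation an omitted covariate does not bias the effect, and a correct standard error includes chance imbalance. What this leaves untouched is imbalance from selecting residents after homes are allocated. Adjusting for measured distress remedies that only in part.
- **Detail may sit elsewhere.** A fuller list may be in an analysis plan that is not shown, and the covariates of the repeated measures ANOVA are unstated. The named list is nevertheless fixed in the article.

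A reader might infer more: that BMI and musculoskeletal history should also be added because "demographic data including age, sex, education, BMI, and history of disease will be collected", and that large gaps in disease mix between arms are to be expected. The document does not support this. It nowhere calls BMI prognostic. It collects history of disease in general, not musculoskeletal history. Its eligibility criteria require musculoskeletal pain of everyone, so a yes/no history may hardly vary. Even for a condition with an assumed 50% prevalence, the SD of the arm difference is √(2 × 0.25 × (1 + 14 × ICC)/60), which is 9.1, 11.9 and 14.1 points at ICC 0, 0.05 and 0.10. A gap of 20 points or more then has a probability of about 3%, 9% and 16%, which is not ordinary.

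**Conclusion.** The point holds as an inexpensive improvement, not as a demonstrated error. The adjusted pain model omits a baseline measure that the protocol collects and whose construct it names as a cause, in a design where that measure may differ between arms by selection. The benefit is modest: close to nil at an extra R² of 0.03 or less, and a power gain of about 2 to 4 percentage points at 0.05 to 0.10 before the cost of the terms, or 1 to 3 after it. These figures rest on the assumed R², a two-sided test and residents treated as independent. The stronger conclusion, that precision is definitely lost or that the primary effect is biased, does not follow from the document. Baseline pain, which enters only through the change score, and home or area, which define the allocation, are larger omissions from the same model.

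**What to change.** In the Data analysis section, add a sentence prespecifying the baseline DASS-21 depression and stress scores as covariates in the pain model, included whatever the observed baseline differences. Specify pre-intervention values: DASS-21 is also a secondary outcome, and follow-up scores may themselves be changed by treatment. Keep the list short, given eight homes, and do not add BMI or a yes/no musculoskeletal history. Baseline pain and home or area need to be accounted for in their own right; this addition does not stand in for them.

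The cost is one sentence, no new data, and two model terms worth about 2% in variance (106/104 = 1.019).

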### Outcomes

The primary outcome of this study is to reduce musculoskeletal pain in the elderly. The secondary outcomes would be reduction in psychological distress (depression, anxiety, and stress) and improvements in beliefs among elderly using the health belief model constructs.

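### The pain-change regression names gender and age group as covariates but not baseline VAS, giving up precision and leaving regression to the mean from any chance baseline difference

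*Protocol article*

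**What the plan says.** The Outcomes section makes pain primary: "The primary outcome of this study is to reduce musculoskeletal pain in the elderly". Under Outcome measures, pain is scored on a VAS graded from 0 to 10, and "The outcomes will be assessed in four points in time: before, immediately, 3, and 6 months after the interventions". A baseline value is therefore planned for every participant.

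The Data analysis section lists four analyses that bear on pain:

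- Within each arm: "Before and after evaluation, intra-group comparisons are determined by paired" *t*-tests.
- Group means: "Independent group means will be evaluated with a 95% confidence interval".
- A regression: "after adjusting for gender and age group, a multivariable linear regression model will be used to examine the combined effects". Its outcome is given in the rest of that sentence: "combined effects of vitamin physiotherapy and social-psychological interventions on changes in pain scores".
- "Repeated measure analysis of variance will also be used", with no factors or covariates stated.

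None of the four is described as adjusting for baseline VAS as a covariate, and none is named as the main analysis.

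**The concern.** The article states both the outcome of the pain regression (change) and its covariates (gender and age group). Baseline pain would ordinarily be expected to predict later pain better than either of these, and it costs nothing to include.

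Subtracting baseline amounts to fixing its coefficient at 1. The coefficient the data would support is nearer to rho, the baseline-to-follow-up correlation, which is below 1. Two things follow. The estimate is noisier than it need be. In addition, if the arms happen to start at different pain levels, the subtraction over-corrects, and the arm with worse starting pain appears to improve more.

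A second, smaller matter is what counts as evidence. A paired test within one arm asks whether that arm changed. Residents are enrolled because they have pain, so both arms may drift downwards without any intervention effect. Because no analysis is ranked, the between-arm estimate should be marked as the one that carries the conclusion.

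**Working it through.** **The plan's own figure.** The Sample size section gives 55 per group at 95% confidence and 80% power, and 60 after allowing 10% dropout. The 55 cannot be reproduced, because no effect size or SD is given. Taking alpha as two-sided 0.05 (an assumption) and inverting the two-means formula gives an implied standardised difference of sqrt(2/55) x (1.960 + 0.842) = 0.534. For dropout, 55/0.9 = 61.1 and 55 x 1.1 = 60.5, so 60 is close enough. The 55 serves below only as a reference point.

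**Inputs.** From the article: change in VAS as outcome; gender and age group as covariates; baseline VAS collected; 55 evaluable and 60 enrolled per group. Not in the article, so assumed: rho from 0.3 to 0.8, equal variance at baseline and follow-up, and independent individuals.

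**Precision.** In units of the VAS variance at one time point:

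- Variance of a change score: 2(1 - rho)
- Residual variance with baseline as covariate: 1 - rho^2
- Adjusted relative to unadjusted: (1 - rho^2) / [2(1 - rho)] = (1 + rho)/2
- Unadjusted relative to adjusted: 2/(1 + rho)

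| rho (assumed) | Adjusted / unadjusted variance | Unadjusted / adjusted variance | Fall in SE | n per arm matching 55 unadjusted | Power if 55 gives 80% unadjusted |
|---|---|---|---|---|---|
| 0.3 | 0.65 | 1.54 | 19% | 36 | 93.5% |
| 0.5 | 0.75 | 1.33 | 13% | 42 | 89.9% |
| 0.7 | 0.85 | 1.18 | 8% | 47 | 86.0% |
| 0.8 | 0.90 | 1.11 | 5% | 50 | 84.0% |

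The fifth column is 55 x (1 + rho)/2, rounded up; for example, 55 x 0.75 = 41.25, so 42.

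**Effect of a chance baseline difference.** Let D be the baseline mean difference, intervention minus control. Given D, the follow-up difference carries rho x D from baseline. The difference in change therefore carries rho x D - D = -(1 - rho) x D. A 1-point difference on the VAS shifts the apparent effect by 0.7, 0.5, 0.3 and 0.2 points at rho 0.3, 0.5, 0.7 and 0.8. The sign is negative: the arm with the higher baseline shows the larger fall.

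**How large D might be.** With 60 per arm and individual randomisation, the SE of D is sqrt(2/60) = 0.18 SD. A one-SE imbalance then leaves 0.18 x (1 - rho), that is 0.13, 0.09, 0.05 and 0.04 SD at the four rho values. The Sampling section describes one home per arm in each of four areas, with 15 residents per group from each. Multiplying the variance by 1 + 14 x ICC gives an SE of D of 0.19, 0.24 and 0.28 SD at assumed ICCs of 0.01, 0.05 and 0.10. Imbalance is thus more plausible under that draw, but the (1 - rho) share need not apply to its between-home part.

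**Do the other listed analyses supply the adjustment?** Group means with a confidence interval are not said to be adjusted. If repeated measures ANOVA takes baseline as one of the time levels, its baseline-to-follow-up group-by-time contrast is again a comparison of change scores.

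**The case against.** Several counter-arguments have force.

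- *A journal article need not give the full model, and the covariate list is not declared exhaustive.* This is fair as far as it goes: an unseen analysis plan could add baseline VAS. But the article does name the outcome and the covariates, so the point rests on stated text. If a fuller plan differs, the two should be brought into line.
- *The change score already uses baseline.* Correct. A reader might infer that baseline pain is ignored and that the raw imbalance passes straight into the estimate. It does not; subtraction removes it. What remains is the over-correction, with the opposite sign.
- *Randomisation removes bias on average.* Also correct. The error exists only conditional on the imbalance that occurs.
- *The formulas are for independent individuals.* This stands. If homes differ in a lasting way, the between-home part of a baseline difference need not regress at the individual rho. The change score could then be nearly right for that part, and adjusting for individual baseline could under-adjust. The tabulated figures do not transfer directly to four homes per arm.
- *The paired tests are not the efficacy test.* A reader might infer that effectiveness will be claimed from significance in one arm and not the other. The article does not say so: it labels these comparisons as within-group and lists between-group means, a regression and repeated measures ANOVA beside them.
- *The model might be read as separating vitamin D, physiotherapy and psychological effects.* The wording speaks of combined effects, which fits a single arm term, so there is no fault to raise there.

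**Conclusion.** The point holds as a specific improvement to the primary-outcome analysis. As written, the pain regression uses baseline VAS by subtraction only. For independent individuals with equal variances, this costs a variance factor of 2/(1+rho), from 1.54 at rho 0.3 down to 1.11 at rho 0.8. The loss is substantial at low correlation and modest at high correlation. Rho is assumed throughout, and the gain may differ under allocation by home.

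Given a chance baseline difference, about (1-rho) of it remains as regression to the mean in favour of the arm with worse starting pain. The documents do not support calling the planned estimate biased on average, nor saying that the within-arm tests will decide the result. They do leave the between-arm estimate unmarked as the primary evidence, which the same edit can settle.

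**What to change.** In the Data analysis section, add baseline VAS as a covariate to the planned pain regression: follow-up VAS, or change in VAS, on arm, baseline VAS, gender and age. With baseline in the model, the two choices of outcome give the same arm effect. State that the adjusted between-arm mean difference with its 95% CI, at each follow-up (immediately, 3 months and 6 months after the intervention), is the evidence of effect. Present the within-arm paired comparisons descriptively only. Treat DASS-21 and HBM scores in the same way, each with its own baseline.

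The cost is a few sentences of analysis wording. Every variable is already collected, and neither the sample size nor the visit schedule changes. How the analysis accounts for nursing home is a separate issue that this edit does not resolve.
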